## Abstract

**Background:**

There is significant evidence on the benefits of comprehensive assessment in older adults. But this evidence is primarily from western countries and in secondary care settings. National policies in India recognize this need and envision community-based screening and facility-based assessment programs integrated into the care pathways for the elderly. However, this is yet to translate into specific interventions, primarily due to lack of complex interventions necessary and evidence of their effectiveness. This study aims to design and pilot an integrated (Community + Facility) Elderly Health Status Assessment and Screening (EHSAS) intervention to improve health outcomes of older adults and assess its feasibility for implementation in Indian rural settings.

**Methods:**

We propose a hybrid design where we will build the complex intervention, develop and validate the tools needed, pilot it using an exploratory cluster randomized trial and evaluate its implementatbility using the Exploration-Preparation-Implementation-Sustainment (EPIS) framework.

**Conclusions:**

This study will fill critical gaps in evidence regarding the effectiveness of geriatric screening and assessment in community and primary care settings in low-middle income countries and provide validated tools and implementation models for adoption into national programs.

**Registration:**

CTRI/2023/07/055661

## Introduction & rationale

The increasingly aging population in low and middle income countries (LMIC) such as India poses unique social and health challenges
^
1
^. This disproportionately impacts rural health systems as over two thirds of older adults in India live in rural areas. Odisha, an eastern state, has one of the highest proportions (>86%) of older adults (aged ≥60 years) living in rural areas in India
^
2,
3
^. This aging population needs community based interventions that include screening and comprehensive assessments aimed at integrated care
^
4
^. One such intervention is Comprehensive Geriatric Assessment (CGA).

CGA is a multidimensional, multidisciplinary process to identify medical, psycho-social, nutritional, and functional needs of older adults and develop an integrated care plan to address these needs
^
5,
6
^. Several systematic reviews have shown that CGA is effective in reducing mortality, disability, and morbidity, and improving clinical outcomes in older adults
^
5,
7–
13
^. However, the evidence on CGA is predominantly from high income countries and targeted at hospitalized older adults
^
5,
14
^. Research on the effectiveness and strategies for CGA in primary care and community settings is lacking, particularly from low- and middle-income countries
^
10
^.

In India, the need for community-based screening and CGA has been recognized in its National Policy for Older People and reflected in the National Program for HealthCare of the Elderly (NPHCE). However, the same has not yet been translated into practice or specific interventions
^
15–
19
^. The primary reason for this evidence-to-practice gap is the conspicuous absence of clearly defined methods for practitioners to perform CGA or implement them into national programs. Further, our recent systematic scoping review revealed there were no multi-dimensional tools that have been validated yet in South Asia, which can be used in such an intervention
^
20,
21
^.

Figure 1 highlights the gaps in care pathways of older adults in India and
Table 1 summarizes the gaps in knowledge identified by previous systematic reviews on the topic and how the proposed study plans to address those gaps.

**Figure 1. f1:**
[figure not shown]
Gaps in the proposed older persons’ care pathway under the National program for Health Care of the Elderly in India (colored boxes) and gaps identified (highlighted).

**Table 1. T1:** Evidence gaps identified and how the study intends to fill those.

Current gaps	How this study will fill those gaps
**Identifying target population**	
**Better methods of identifying the ideal target population** ** for CGA ^ 5, 12, 23 ^ **	Evidence on effectiveness of community-based screening to identify those in need of a CGA.
**Geriatric Screening and assessment**	
**No locally validated tools to use for CGA ^ 20, 21 ^ **	Design and validate a set of tools that can be used for CGA in India (and possibly other South Asian countries)
**Limited evidence on role of CGA in LMICs ^ 5, 7– 14 ^ **	Evidence (from LMIC) on effectiveness of multidisciplinary screening in community and CGA in primary care settings.
**Interventions based on CGA**	
**Lack of standardization in the geriatric screening and** ** assessment processes ^ 20, 21, 23 ^ **	Standardize the assessment process in the context of the national program (NPHCE) in India
**No CGA-based interventions or evidence on their feasibility/** **effectiveness in primary healthcare settings ^ 5, 12, 24 ^ **	Build and evaluate the feasibility and effectiveness of a CGA-based intervention in rural community and primary care settings.
**Outcome measures**	
**Limited evidence on the role on Patient Reported Outcome** ** Measures (PROMs) in CGA ^ 5 ^ **	Evaluate effect of CGA on PROMs (quality of life and self-rated health)
**Implementation designs**	
**Inadequate evidence on feasibility of integrating CGA-** **based interventions into existing programs ^ 5 ^ **	Evaluate the acceptability and feasibility of the implementation process in context of existing national programs (e.g. NPHCE)

There is a need for an approach to improve health outcomes among older adults in India by developing methods for assessment and implementation, and building capacity in the healthcare of older people.

### Research questions

▪ What is the feasibility and likely benefit of an integrated Elderly Health Status Assessment and Screening (EHSAS) intervention in improving health outcomes among older adults residing in rural areas of Odisha?▪ What factors could facilitate the future implementability of such an intervention?

### Objectives

a. To design and validate a complex Elderly Health Status Assessment and Screening (EHSAS) intervention for community-based screening and primary healthcare based CGA in older adults aged ≥60 years.b. To test the feasibility and likely effectiveness of this intervention, by a phase-II exploratory cluster randomized controlled trial (RCT), on the quality of life among adults aged ≥60 years in rural areas of Tigiria, Odisha.c. To assess the acceptability of the intervention among service providers and clients and identify the factors that could influence its implementation.

### Work that has led up to this protocol

Work at the Model Rural Health Research Unit (MRHRU), operated by the host institute at the proposed study site in Odisha, forms the foundation for this proposal
^
22
^. A Health and Demographic Surveillance System named the DISHA cohort, that includes approximately 20,000 families from 48 villages, has shown the changing demographic trends of an aging rural population and the subsequent health and social challenges.

This led to the establishment in 2018 of a prospective cohort under the AHSETS study that aims to evaluate the prevalence and interrelationships between multiple domains of health in older adults. The baseline data collection was completed in 2019–2020 for 725 randomly selected rural older adults (aged between 60–106 years, mean = 70 years, 48% females) and we plan to follow them up longitudinally for 2 years
^
25–
29
^. The AHSETS study has provided evidence of high disease burden (e.g. multimorbidity, disability, frailty, elder abuse) and on the interplay of various physical, psycho-social, and functional domains of health. This has emphasised the need for CGA in rural community settings to identify and manage complex health issues.

The AHSETS study also identified challenges in the assessment and management of older people with complex health needs, in particular the length of time for such detailed assessments and the use of separate and disjointed tools (often with redundant concepts) built for use in a different context. This led to a search for multidimensional and locally relevant health assessment tools. Subsequently, we undertook a systematic scoping review to identify the tools validated for use in South Asian older adults. However, we could not find a single tool that had all the dimensions of CGA
^
20,
21,
30
^.

## Methods

We propose the development and evaluation of a complex CGA-based intervention using the UK Medical Research Council (MRC) framework
^
31–
33
^. The methodology is presented in three broad steps outlined in
Figure 2 and are further elaborated below:

**Figure 2. f2:**
[figure not shown]
Outline of the proposed study design.

1.  Intervention development (EHSAS)2.  Piloting of the intervention3.  Implementation model development and evaluation of feasibility

### Intervention development (EHSAS)

i. 
Identification of the evidence base
▪ 
*Umbrella review:* We will carry out an umbrella review to synthesize evidence from existing systematic reviews, e.g.
5,
7,
10 focussing on lessons for LMIC and primary care/rural settings. We will follow the guidance provided by the Cochrane Handbook for this umbrella review
^
34
^.▪ 
*Scoping review for screening tools:* We have recently completed a review which could not identify any appropriate and comprehensive tools, therefore a new tool needs to be developed and validated for use in the intervention phase
^
21
^.▪ 
*DISHA cohort:* We will carry out a descriptive analysis of the socio-demographic and health parameters of older adults collected in the DISHA cohort to describe the characteristics of the target population.▪ 
*Expert consensus:* The above evidence will be summarized and shared before a panel of experts consisting of geriatricians, public health specialists, primary care physicians, researchers, and psychologists, from both India and UK. Using multiple rounds of consultations, we will attempt to reach a broad consensus on the following characteristics of the intervention package:- Components of intervention- Parameters of intervention- Delivery methods- Levels of implementation.

ii. 
Development and validation of the tools: Two tools will be developed and validated:○ EHSAS-C → for community-based multidisciplinary screening○ EHSAS-F → facility based comprehensive assessment (for those identified by screening)

These tools will form the basis of the subsequent steps in the intervention. The screening toll will identify the older people from the community who are most likely to benefit from a facility based CGA. The facility based tool will focus on care coordination at the primary healthcare level, while covering all domains of CGA in a more detailed assessment and care planning format.

The following 9 steps (in 3 phases) outlined by Boateng
*et al*. as the best practices in tool development and validation will be followed (
Table 2):
^
35
^

**Table 2. T2:** The proposed tool development and validation procedures.

Activity		Purpose	Methods
**Phase-I: Item** ** development**	Domain Identification & Item generation	Identify boundaries of the domains and fitting constructs	The domains and constructs relevant for CGA is well established ^ 5 ^. We will use deductive methods and existing wider datasets and tools: AHSETS study and the Longitudinal Aging Study of India (LASI) that are available with us to generate preliminary items lists ^ 29, 37, 38 ^.
	Content validity	Evaluation of relevance and technical quality of the constructs by experts and representativeness of actual experience from target population	Content validity ratio and Cohens kappa (n= 7-9 domain experts) Face validity (n=10-12 end users)
**Phase-II: Scale** ** development**	Pre-testing	Assess the extent to which questions reflect the domain of interest and answers produce valid measurements	Cognitive interviews (n=10-12 clients in 2 rounds)
	Data collection	Ensure adequate data for scale development and validation	Cross-sectional surveys (n=200, from the AHSETS cohort x 2 rounds, 3 months apart)
	Item reduction	To evaluate item difficulty, discrimination, correlation between items and missing answers	Item difficulty index, inter-item communalities, item-total correlations.
	Factor analysis	Determine the optimal number of factors/domains that fit a set of items	Exploratory factor analysis
**Phase-III: Scale ** **evaluation**	Tests for dimensionality	Identify latent structure of items and their underlying relationships	Confirmatory factor analysis
	Tests for reliability	Assess internal consistency and repeatability	Cronbach’s alpha, test-retest reliability over two time points
	Tests for validity	Establish convergent and discriminant construct validity	Estimate the strength and direction of relationship of constructs with similar tools using multi-trait multi-method matrix

iii. 
Development of theoretical framework

From the existing evidence base, we start with a preliminary theoretical framework (given below in
Figure 3) for the possible mechanism of action and efficacy of EHSAS intervention.

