## Data Availability

No underlying data are associated with this article. figshare: Suppl file.dox.
https://doi.org/10.6084/m9.figshare.23918490.v1 This project contains the detailed data analysis plan. Data are available under the terms of the
Creative Commons Attribution 4.0 International license (CC-BY 4.0). Complete data access will be only available to the core team of the project at ICMR-RMRC. Deidentified data will be shared upon reasonable request for the same from external agencies, in accordance with ICMR data sharing policy. A structured form will be developed for this and an end user licence agreement will be executed with these agencies/individuals. Data security will be ensured by using dedicated in-house servers located at the National Data Centre of IT ministry, Govt. of India, which handles these servers for the host institute. Access to this data will be controlled and a log of the same will be maintained and audited regularly. Direct access will not be available outside India. Data confidentiality will be ensured rigorously by deidentifying the data at the earliest chance. Data that will be shared with external agencies/individuals, or metadata used for interim analysis, or final analysis, will not consist of any participant identifiers. Approval for the data management policy will be sought from the institutional ethical committee of ICMR-RMRC. The findings of the study will be reported following the recommendations of the CONSORT statement specific for cluster RCTs.

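### Table 2 names Cohen's kappa, a two-rater statistic, for ratings by 7-9 experts; the form of kappa should be one defined for the panel, preferably item by item

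*Protocol article*

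**What the plan says.** Objective (a) of the protocol article is "To design and validate a complex Elderly Health Status Assessment and Screening (EHSAS) intervention". Under Intervention development (EHSAS), the article says "Two tools will be developed and validated": EHSAS-C for community screening and EHSAS-F for facility-based assessment. Table 2 sets out the steps.

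- **Content validity (Phase I).** The stated purpose is "Evaluation of relevance and technical quality of the constructs by experts and representativeness of actual experience from target population". The method for the expert part is "Content validity ratio and Cohens kappa (n= 7-9 domain experts". The cell does not say how kappa is extended beyond two raters, which rating scale is used, or what value would lead to dropping an item.
- **Source of items (Phase I).** The article states "The domains and constructs relevant for CGA is well established" and derives preliminary item lists from existing datasets and tools.
- **Reliability of the tools (Phase III).** This is a separate row: "Cronbach’s alpha, test-retest reliability over two time points". Kappa is not named there.

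The Data Availability section refers to a supplementary file, which is not shown: "This project contains the detailed data analysis plan".

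**The concern.** The statistic and the number of raters stand in the same cell and do not fit each other. Cohen's kappa is built from the cross-classification of two raters, so a panel of 7-9 has no single Cohen's kappa.

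The analyst will therefore have to substitute something, and the likely choices carry a known weakness. Both the mean of the pairwise kappas and Fleiss kappa are computed over the whole item set, and both correct for chance using the overall share of ratings in each category. If almost all ratings are in the relevant category, expected agreement is nearly as high as observed agreement, and kappa falls towards zero however well the experts agree. At stake is the figure published as evidence that experts agreed on the content of the two tools.

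**Working it through.** The protocol gives no kappa value or cut-off for this step, so there is no figure to reproduce.

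**Inputs.** From Table 2: 7 to 9 experts. Assumed, because the article does not give them: a binary relevant / not relevant rating; sound items endorsed with probability 0.90 or 0.95; poor items endorsed with probability 0.10 or 0.40. The simulations used 40 items and 200 panels per setting.

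**1. Number of pairs.** n(n-1)/2 = 21, 28 and 36 for n = 7, 8 and 9.

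**2. One dissent on every item (exact).** Observed pairwise agreement is P = C(n-1,2)/C(n,2). Expected agreement is Pe = p² + (1-p)², with p = (n-1)/n. Fleiss kappa = (P - Pe)/(1 - Pe).

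For n = 8: P = 21/28 = 0.750; Pe = 0.875² + 0.125² = 0.781; kappa = (0.750 - 0.781)/(1 - 0.781) = -0.14. For n = 7 and 9, agreement is 0.71 and 0.78 and kappa is -0.17 and -0.13. If all experts endorse all items, P = Pe = 1 and kappa is 0/0.

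**3. All items equally relevant, random dissent.** Expected pairwise agreement is p² + (1-p)²: 0.82 at p = 0.90 and 0.905 at p = 0.95. Simulated Fleiss and mean pairwise kappa are about 0.00 in both cases. At p = 0.95, 95% of simulated panels gave Fleiss values between roughly -0.05 and 0.09.

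**4. Mixed item pool.** In expectation, Fleiss kappa is approximately the between-item variance of the endorsement probability divided by m(1-m), where m is the mean endorsement. Take 10% of items with probability 0.10 and 90% with 0.95. Then m = 0.865; variance = 0.1 × 0.9 × 0.85² = 0.0650; m(1-m) = 0.1168; kappa = 0.0650/0.1168 = 0.56. The simulation also gives 0.56. Simulated results, with sound items at 0.95:

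| Share of poor items | Kappa, poor items endorsed by 10% | Kappa, poor items endorsed by 40% |
|---|---|---|
| 5% | about 0.41 | about 0.20 |
| 10% | about 0.56 | about 0.29 |
| 20% | about 0.67 | about 0.36 |
| 30% | about 0.71 | about 0.37 |

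So the collapse in steps 2 and 3 depends on a nearly uniform pool.

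**5. Item-level indices.** With a of n experts endorsing an item: I-CVI = a/n; content validity ratio = (a - n/2)/(n/2); modified kappa = (I-CVI - pc)/(1 - pc), with pc = C(n,a) × 0.5^n. For 7 of 8: pc = 8/256 = 0.031 and modified kappa = (0.875 - 0.031)/(1 - 0.031) = 0.87.

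| Panel, one dissent | I-CVI | Content validity ratio | Modified kappa |
|---|---|---|---|
| 6 of 7 | 0.86 | 0.71 | 0.85 |
| 7 of 8 | 0.88 | 0.75 | 0.87 |
| 8 of 9 | 0.89 | 0.78 | 0.89 |

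With no dissent, all three indices equal 1.00. They are defined for any panel size and do not depend on how the other items are rated.

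**The case against.** The strongest reply is that this is shorthand. Table 2 condenses a cited nine-step guide, a detailed analysis plan exists elsewhere, and a journal article may leave the exact form of kappa to it. That stands for the rating scale, the cut-off and the computing details, and none of these is raised here as missing. It does not cover the statistic that is named: it does not fit the number of raters beside it, and the cell should agree with whatever the fuller plan does.

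Second, the article does not establish a nearly uniform item pool. It calls the domains well established, but the item lists are preliminary, an item-reduction step follows, and the background section describes existing tools as overlapping and made for other settings. A mixed pool is quite possible, and set-level kappa then does not collapse. This stands, and it makes the understatement conditional.

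Third, the content validity ratio is already planned. Taken from the same endorsement count it equals 2 × I-CVI - 1, so the item-level index and modified kappa add no new data. This also stands. Their advantage is that they give the kappa component a form that can be computed for 7-9 experts.

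A reader might go further and infer that sound items would be rejected, or that the tools would look unreliable. The documents do not support either. A set-level kappa cannot reject a single item, the content validity ratio works item by item, no kappa cut-off is stated, and tool reliability is judged separately by Cronbach's alpha and test-retest.

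**Conclusion.** The point holds in a limited form. Cohen's kappa cannot be applied as written to 7-9 experts, which follows from the cell itself and needs no assumption. The further risk, that a pairwise or set-level substitute understates expert agreement, is real only if nearly all items are rated relevant. In that case kappa is about zero, slightly negative or undefined while agreement is 75% to 91% in the 8-expert example and the two uniform-pool settings. With 5-30% clearly poor items it is about 0.4-0.7, and with milder poor items about 0.2-0.4. These figures rest on an assumed binary scale, item count and endorsement rates.

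The consequence is confined to how expert agreement is reported during tool development. The trial's primary outcome, the quality-of-life score, is not touched. A reader might also expect a particular significance-based rule for retaining items; the documents fix no such rule, and choosing one would be a preference rather than the correction of an error. Severity is minor.

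**What to change.** In the content-validity row of Table 2, replace Cohen's kappa with the item-level content validity index and its chance-corrected (modified) kappa, calculated for the number of experts who actually rate, and report both beside the content validity ratio. If a set-level multi-rater kappa is also wanted, name its form and give raw pairwise agreement with it, so that a low value from a uniformly endorsed pool is not misread. Bring the supplementary analysis plan into line if it differs.

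The cost is one table cell and a short calculation on ratings that will be collected anyway. No further experts, items or participants are needed.

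### The only test-retest interval given for the new tools is 3 months, so repeatability will be mixed with real health change and will tend to be understated

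*Protocol article*

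**What the plan says.** Under Intervention development (EHSAS), Table 2 has one row for quantitative data collection on the scales: "Cross-sectional surveys (n=200, from the AHSETS cohort x 2 rounds, 3 months apart"). Its stated purpose is "Ensure adequate data for scale development and validation", so one source serves both tasks.

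The analyses listed after it are:
- Phase II: item reduction (difficulty index, communalities, item-total correlations), then "Exploratory factor analysis".
- Phase III: "Confirmatory factor analysis", Cronbach's alpha, "test-retest reliability over two time points", and validity by a multi-trait multi-method matrix.

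Table 2 names no second sample, shorter retest interval, change question or restriction to stable respondents. It does not say whether the two rounds interview the same people, or which round serves which factor analysis.

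The section on preparatory work describes the source cohort: "The baseline data collection was completed in 2019–2020 for 725 randomly selected rural older adults", with a mean age of 70, and "evidence of high disease burden (e.g. multimorbidity, disability, frailty, elder abuse") among its findings.

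**The concern.** Test-retest reliability is meant to measure how far a score varies when the person has not changed. The EHSAS tools measure health status. Over 3 months, some members of a cohort with this disease burden will truly improve or decline, and the retest coefficient counts that change as unreliability. A modest coefficient could then mean a noisy tool or a tool that correctly registers change, and the plan as printed cannot say which.

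There is a related question about structure. If factors are chosen in one set of people and then tested in the same people, chance features of that sample carry over and the confirmation is weaker than it looks.

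Validating the tools is part of objective (a), the abstract promises validated tools for national programmes, and the later steps of the intervention are built on them.

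**Working it through.** The article gives no derivation for the 200, no target reliability and no stability figure, so there is no stated result to reproduce. Three checks follow.

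**1. Effect of the 3-month interval**

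Assume equal score variance at both rounds and independent measurement errors. Then:

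expected retest correlation = true reliability × stability of true health over the interval

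Both inputs are assumptions. The interval is from Table 2.

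| Assumed reliability | Stability 1.00 | 0.95 | 0.90 | 0.80 | 0.70 |
|---|---|---|---|---|---|
| 0.90 | 0.90 | 0.855 | 0.81 | 0.72 | 0.63 |
| 0.80 | 0.80 | 0.76 | 0.72 | 0.64 | 0.56 |
| 0.70 | 0.70 | 0.665 | 0.63 | 0.56 | 0.49 |

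For reliability 0.90 and stability 0.80 to 0.90, this gives 0.90 × 0.80 = 0.72 and 0.90 × 0.90 = 0.81.

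An observed 0.72 arises both from 0.90 × 0.80 and from 0.80 × 0.90. Two time points with no information on change cannot separate these cases. Sample size does not help: at n = 200 the Fisher-z 95% interval around 0.72 is about 0.65 to 0.78, which is centred on the attenuated value and excludes a true 0.80 or 0.90.

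**2. What the two rounds can support**

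- *Same 200 people twice:* a 200-person retest is possible. An independent confirmatory analysis would need a split, about 100 + 100.
- *Two different sets of 200:* the confirmatory analysis is independent, but no retest is possible.
- *Two independent random draws from 725:* expected overlap is 200 × 200 / 725 ≈ 55 people, which allows a small retest and a largely independent confirmation.

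No reading gives both a full-sample independent confirmation and a 200-person retest, so the article needs to say which is intended.

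**3. How much reuse matters for structure**

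A simulation (1,000 replicates, n = 200) assumed 20 items, one true factor with loading 0.5, and 60% of each item's unique variance stable. A spurious second factor was picked in round 1, and the excess correlation among its four leading items was then measured in three data sets:

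| Data used to confirm | Excess correlation |
|---|---|
| Same data | 0.035 |
| Same people at round 2 (stability 0.80 to 1.00) | 0.007 to 0.009 |
| New people | about 0 (−0.001 to 0.002) |

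Reusing the same round is the main problem. Using round 2 removes most of the bias, and new people remove it all.

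**The case against.** **The same 200 people.** A reader might infer that both factor analyses and the retest all use the same 200 people. The text does not say so. It calls the surveys cross-sectional and assigns no round to either factor analysis. A retest needs only some repeat respondents. The data availability statement points to a detailed analysis plan in a supplement that is not shown, and a split or assignment could be there. This objection stands, and it is why the factor-analysis part is conditional and secondary. Even if the people are the same, the simulation shows that a round-2 confirmation leaves little bias.

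**Wrongly dropped items.** A reader might also infer that an understated retest would cause items to be wrongly dropped. Table 2 does not support that. Item reduction is a Phase II step with its own criteria, test-retest comes later, and no retest cut-off is stated.

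**Size.** The cohort is a random rural sample in which frailty is one of several burdens, not a frail population, and its 3-month stability is unknown. The magnitudes are therefore illustrations. Cronbach's alpha, computed within a round, is not disturbed by change between rounds. It measures internal consistency, however, and does not replace a retest.

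**Left to the analysis plan.** A stable-respondent analysis could be specified there, but such a plan cannot shorten the interval between rounds, and it can select unchanged respondents only if a measure of change is collected. The retest point survives this objection.

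**Conclusion.** The retest point holds. The only two time points in Table 2 are 3 months apart, and nothing there separates error from true change, so repeatability will tend to be understated. The direction follows from the design, provided that errors are independent between rounds. The size rests on assumed stability: reliability 0.90 would show as 0.72 to 0.81 at stability 0.80 to 0.90, and would show no loss if health were perfectly stable.

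The structure point holds only conditionally. No separate sample is named for the confirmatory analysis, and if the same people serve both analyses the structure is not independently confirmed.

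The consequence is limited to the claim that the tools are validated. It does not reach the randomisation, the EQ5D primary outcome or the pilot's feasibility measures. The change is worth making because it is cheap.

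**What to change.** **Retest.** Add one global-change question at round 2. Report test-retest reliability in respondents reporting no change, alongside the figure for all respondents. Alternatively, re-interview a subset of round-1 respondents at a shorter interval. The study status section says that recruitment for tool development has started, so the shorter-interval option depends on how far round 1 has gone. The change question needs only that round 2 is still ahead.

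The cost is precision. With 95% limits tanh(atanh r ± 1.96/√(n − 3)) at r = 0.80:

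| Retest n | 95% interval |
|---|---|
| 200 | 0.744 to 0.845 |
| 100 | 0.716 to 0.861 |
| 50 | 0.671 to 0.882 |

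Keeping the all-respondent figure limits that loss. Self-reported change is also an imperfect marker of stability.

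**Structure.** State whether the two rounds interview the same people. Run item reduction and the exploratory analysis on round 1 and the confirmatory analysis on round 2, preferably in AHSETS members not used for the exploratory step. On the 2019–2020 baseline count, 725 − 200 = 525 members lie outside the first sample. Attrition since then will have reduced that number, and each new respondent who replaces a repeat one shrinks the 3-month retest. If new respondents are not feasible, describe the confirmatory analysis as not independent.
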